### **6.3.1 Surgery**

Study surgeons at each recruiting site will administer the surgical rotator cuff repair/debridement for those subjects in the operative arm of the study recruited from their site. Surgery should be scheduled to occur within 8 weeks after randomization to the operative treatment arm. If surgery occurs later than 8 weeks after randomization, it will be considered a protocol deviation.

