### 12.2 Final Analysis Plan

**Overview:** We are planning a trial where patients will be randomly assigned in equal proportion to operative or non-operative care.

**Primary Endpoint:** The primary outcome measure is SPADI, and the primary endpoint is the change in SPADI at 12 months relative to baseline. SPADI is measured on a scale of zero to 100, with lower scores for better outcomes. SPADI is a reliable and valid measure of shoulder function.

**Secondary Endpoint(s):** ASES-SF, cross-sectionally and longitudinally over time.

**Analysis Population:** We define the intent-to-treat (ITT) population as the group of patients randomized to a treatment arm regardless of any other consideration.

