#### 12.2.1 Primary Analysis

The primary analysis will be conducted on the intent-to-treat (ITT) population as defined above. The distribution of 12-month change in SPADI, stratified by treatment

arm, will be summarized graphically with histograms, boxplots, and plots of CDFs as appropriate. Our primary analysis for testing the 3 specific hypothesis in section 12.1 will be conducted in the context of a mixed model. That model is,

$$y_{ij} = \beta_0 + \beta_1 I_{\{TRT_i=op\}} + \beta_2 t_{ij} + \beta_3 I_{\{TRT_i=op\}} t_{ij} + \beta_4 (tearsize_i) + \beta_5 (age_i) + \beta_6 (I_{\{TRT_i=op\}} * tearsize_i) + \beta_7 (I_{\{TRT_i=op\}} * age_i) + u_i + e_{ij}$$

where  $y_{ij}$  represents the change in SPADI from baseline for participant  $i = 1, \dots, n$  at time  $j = 3, 6, 12$  months who was assigned to management arm  $TRT_i$  ( $I_{\{TRT_i=op\}} = 1$  if participant  $i$  is on the Operative arm and 0 otherwise).  $\beta_0$  is the intercept,  $\beta_3$  is differential change in SPADI score over time due to treatment (i.e., the treatment effect over time; assumed linear here but it will be modeled flexibly as needed),  $\beta_4$  and  $\beta_5$  are the effects of tear size and age at the beginning of treatment, and  $\beta_6$  and  $\beta_7$  are the tear size and age interactions with treatment that potentially will help identify those patients most likely benefit from therapy. The first 8 terms represent fixed effects. The last 2 terms represent a patient specific random intercept to model the effects of study site and residual error, respectively. The estimate of interest from this longitudinal model is the predicted differential in 12-month SPADI change ( $\Delta\Delta SPADI_{12}$ ; 1st  $\Delta$  is for treatment change, 2nd  $\Delta$  is for 12-month change), which is typically estimated as a contrast or difference in predicted 12-month SPADI change.

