A directly parallel analysis will also be conducted, where  $y_{ij}$  represents SPADI for participant  $i = 1, \dots, n$  at time  $j = 3, 6, 12$  months with baseline SPADI as a covariate. In the first model, analyses might lead to a statement such as “Pain and function improved over 12 months in the operative (non-operative) care group 11 points more on average compared to patients treated with non-operative (operative) therapy. In the second model, analyses may lead to a statement such as, “At 12 months, mean SPADI scores were 11 points lower in the non-operative (or operative) group.”

A restricted cubic spline may be fit for continuous covariates to allow for nonlinearity. Further, we will examine different parameterizations of “time” to appropriately capture longitudinal trends (e.g., we might use a time-squared term or let time be categorical). To account for site-to-site variation, the model will include either a fixed effect or random effect for sites (not shown here). The choice between a fixed and random effect often generates debate. While our general preference is to use a random effect, and that is our stated plan here, we realize that with multiple sites the resulting random effect estimates could be unstable due to imbalance in the number

of recruitments, especially if there are pronounced aggregate covariate dissimilarities across sites. In such a case, we will use a fixed effect for site. For completeness, we will report the unadjusted estimates for  $\Delta\Delta\text{SPADI}_{12}$  that results when  $Z_i$  is removed from the model. Note that in a randomized study the purpose of covariate adjustment in a regression model is to obtain unbiased estimates of effects accounting for the enormous variation typical of longitudinal studies.

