### **12.4 Model Assessment and Sensitivity Analyses**

**Treatment of Crossovers and Missing Data:** Although we expect that a significant but manageable number (8% in our observation study) of patients receiving PT only (non-operative treatment) will request surgery (operative treatment), our analytical strategies presented below will also account for the potential of high crossover rates. We order our analyses as follows: First, our primary model will be a strict intent-to-treat analysis, wherein patients who choose to crossover to surgical treatment will have post-surgical outcomes attributed to the treatment arm as randomized. Second, we will treat crossovers as dropouts at the time of crossover and treat the resulting data as missing to be evaluated according to Rubin's classification of missing data and their appropriate analyses. Our sample size estimates illustrate that these analyses have good power, even in the presence of significantly high rates of missing/crossover data, and we believe they will provide the best estimates of treatment and covariate effects. Third, we will assign a treatment effect of zero to each crossover patient. This approach assigns an appropriate penalty to the non-

surgical treatment for having failed that patient. This approach will produce appropriately conservative statistical tests and preserve study power.

**Assessing Model Fit:** The assessment of model fit is indispensable for model development and implementation. Non-linear predictor rescaling, in the form of restricted cubic splines, will be evaluated and models compared using Akaike criteria. Multivariate association and missing data patterns will be evaluated using trellis graphics and clustering algorithms. Such summary analyses may inform sensitivity analyses with respect to modeling assumptions, rescaling of predictors (e.g., restricted cubic splines), and co-linearity. We will repeat these analyses for the secondary outcome (ASES-SF). Along with standard goodness-of-fit and residual analysis, we will perform model validation and calibration using bootstrap methods as discussed in Harrell.

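### The primary 12-month contrast is written with a straight line in time and no rule for leaving it, so early treatment differences can leak into the 12-month result

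*Protocol*

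**What the plan says.** Protocol Section 12.2 states that "the primary endpoint is the change in SPADI at 12 months relative to baseline". Section 12.2.1 then writes out a mixed model for change from baseline at 3, 6 and 12 months, with a linear time term, a linear treatment-by-time term and a patient random intercept. It adds: "The estimate of interest from this longitudinal model is the predicted differential in 12-month SPADI change".

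The treatment-by-time term is described as "assumed linear here but it will be modeled flexibly as needed". Later in the same section the plan says "we will examine different parameterizations of" time, and that "we might use a time-squared term or let time be categorical". No criterion, order or timing is attached to this. For the site effect, by contrast, the same section gives both a default (random) and the circumstance in which it would be abandoned (unstable estimates).

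Three facts elsewhere in the protocol bear on the point:

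- Section 6.3.1: "Surgery should be scheduled to occur within 8 weeks after randomization to the operative treatment arm".
- Sections 6.1.2 and 6.3.2: post-operative rehabilitation lasts about 4 months. The non-operative programme lasts about 3 months.
- Section 5.4.2: the arms are not masked.

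**The concern.** A straight line in the treatment difference is a strong assumption on this schedule. Questionnaires are timed from randomization (Section 7.4.1). A patient operated on at week 8 is about 5 weeks past surgery at the 3-month questionnaire (13 - 8 weeks), while a non-operative patient who started promptly is finishing the programme. The difference between arms could well change direction or level off over the year.

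Under the line, the 12-month estimate is a weighted mix of all three visits, so an early difference moves the 12-month answer. If the line is not kept, the primary estimate depends on a choice with no stated rule, made by people who may know the allocation. The p-value for Hypothesis 1 is at stake, more than the clinical size of the effect.

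**Working it through.** **Inputs from the protocol.** SDs of 12-month change 21.55 (n=45) and 19.14 (n=27), and 24.2 overall (Section 12.3.1); meaningful difference 10 points (12.3.2); 350 per arm and two-sided 0.05 (12.3.3).

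**Assumptions, not in the protocol.** The size of any month-3 or month-6 difference, a common SD at each visit, between-visit correlation 0.3 to 0.7, complete data, nominal visit times.

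**Reproducing the plan's figure.** Pooled SD = sqrt[(44 x 21.55² + 26 x 19.14²)/70] = 20.69. For a t-test of a 10-point difference, the noncentral t gives 90% power at 91 per arm (0.9003), as Section 12.3.3 states. The pooled SD is therefore a fair basis for what follows.

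**Weights under the line.** For t = 3, 6, 12 the mean is 7 and the sum of squares is 16 + 1 + 25 = 42. The weight of visit t in the prediction at 12 is 1/3 + (12 - 7)(t - 7)/42:

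- month 3: 14/42 - 20/42 = -1/7
- month 6: 14/42 - 5/42 = 3/14
- month 12: 14/42 + 25/42 = 13/14

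With a random intercept and complete data, generalized and ordinary least squares give the same weights. Let D be the operative minus non-operative change, so positive means surgery is worse. The contrast is -(1/7)D3 + (3/14)D6 + (13/14)D12, and its departure from D12 is -(2D3 - 3D6 + D12)/14. When D12 = 0, a false benefit for surgery arises only if D3 > 1.5 x D6.

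**Standard errors at 350 per arm.** Categorical visit: 20.69 x sqrt(2/350) = 1.564. Line: 1.524 to 1.547 for correlation 0.3 to 0.7.

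**Results when the true 12-month difference is zero:**

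| D3, D6 (assumed) | Line reports at 12 months | Two-sided error, SD 20.69 |
|---|---|---|
| 5, 0 | -0.71 | about 0.075 |
| 10, 0 | -1.43 | 0.152 to 0.155 |
| 15, 0 | -2.14 | 0.283 to 0.290 |
| 10, 5 | -0.36 | 0.056 |
| 15, 10 | 0 | 0.050 |
| 10, 10 | +0.71 (against surgery) | about 0.075 |

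With SD 24.2, the first three errors are about 0.07, 0.12 to 0.13, and 0.22.

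**If the fit is checked.** The curvature contrast is 2D3 - 3D6 + D12. With a 10-point deficit at month 3 only, a test of it has at least 98% power (SD 20.69). An AIC-type rule drops the line in over 99% of simulated trials, and the error returns to about 0.05. With a 5-point deficit the power is 53 to 88%, so the line may survive, but the bias is then only 0.71.

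**If the choice is free.** Taking the smaller of the linear and categorical p-values gives error 0.057 to 0.060 with no effect at any visit, and about 0.18 with the 10-point month-3 deficit.

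**The case against.** The strongest reply is that the protocol does not insist on the line. It calls it provisional and names categorical time, so the 0.15 and 0.29 describe a model that would probably be dropped if fit were checked. That stands. A reader might infer that the protocol locks in a straight line, and the text does not support this.

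The direction is not fixed either. A reader might infer from the surgical timetable that the bias must favour surgery. But surgery at week 8 followed by about 4 months of rehabilitation runs to about month 6, so a deficit may persist there, and then the bias vanishes or turns against surgery. Week 8 is also the outer limit rather than the typical case, and the protocol gives no month-3 or month-6 SPADI data.

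A reader might also take it that AIC selects the primary time form. Section 12.4 says only: "Non-linear predictor rescaling, in the form of restricted cubic splines, will be evaluated and models compared using Akaike criteria". That concerns the rescaling of predictors and is not tied to the time term. That the choice would follow sight of the data is a fair inference from the wording, but no timing is stated.

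The room for selection is limited. With three nominal visits, a time-squared term interacted with treatment gives the same 12-month contrast as categorical time, so the named forms reduce to two.

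Finally, the time form could be settled in an SAP that is not shown. This does not remove the point, because the protocol itself states a default that can bias Hypothesis 1 and an open-ended way of leaving it.

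**Conclusion.** The point holds in a limited form. As written, the primary estimate is a linear-in-time prediction into which month 3 enters with weight -1/7, and the plan gives no rule for replacing the line. The bias is about 1.4 points per 10 points of a deficit confined to month 3. That is small against the 10-point meaningful difference, but enough at 350 per arm to triple the nominal error to about 0.15. It could favour surgery, be absent, or run against surgery, depending on month 6.

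If the line is abandoned after a fit check, the bias largely goes. What remains is an unspecified choice, costing up to about one percentage point of error with no effect at any visit, and more only with both an early deficit and deliberate selection of the smaller p-value. All the deficit sizes are assumptions. No fault in the random intercept has been shown, so a demand for unstructured covariance would be a preference and is not part of this conclusion.

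**What to change.** Commit now, in Section 12.2.1, to visit as a categorical factor (3, 6, 12 months) with treatment-by-visit terms as the primary model, and state that Hypothesis 1 is tested by the 12-month contrast. Label linear, quadratic or spline time, using actual completion dates as Section 7.4.1 foresees, as sensitivity analyses.

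Categorical time is already on the sponsor's list, so this changes wording only. Under the assumptions above, the SE rises from 1.52-1.55 to 1.56, about 1 to 3%. Power for a 10-point difference at 350 per arm stays above 99.9%.

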### 12.2.2 Secondary Analyses

Secondary analyses will be based a more general model denoted,

$$y_{ij} = \beta_0 + \beta_1 I_{\{TRT_i=Op\}} + \beta_2 t_{ij} + \beta_3 I_{\{TRT_i=Op\}} t_{ij} + \gamma Z_i + u_i + e_{ij}$$

where  $y_{ij}$  represents the change in ASES-SF (or any other outcome metric) from baseline for participant  $i = 1, \dots, n$  at time  $j = 3, 6, 12$  months who was assigned to management arm  $TRT_i$  ( $I_{\{TRT_i=Op\}} = 1$  if participant  $i$  is on the Operative arm and 0 otherwise) and who has a  $k$ -dimensional vector of covariates  $Z_i$  (e.g., gender, mental health inventory, fatty infiltration, etc.) with effect parameters  $\gamma_k$ .  $\beta_0$  is the intercept, and  $\beta_3$  is differential change in ASES score over time due to treatment (i.e., the treatment effect over time; assumed linear here but it will be modeled flexibly as needed). As in section 12.2.1, the last 2 terms represent a patient specific random intercept and residual error, respectively. The estimate of interest from this longitudinal model is the predicted differential in 12-month ASES-SF

change ( $\Delta\Delta\text{ASES-SF}_{12}$ ; 1st  $\Delta$  is for treatment change, 2nd  $\Delta$  is for 12-month change), which is typically estimated as a contrast or difference in predicted 12 month ASES-SF change.

Similar to the setting described in section 12.2.2 directly parallel analyses will also be conducted, where  $y_{ij}$  represents ASES-SF (or other secondary outcomes) for participant  $i = 1, \dots, n$  at time  $j = 3, 6, 12$  months with baseline ASES-SF as a covariate. Differential inference between these two sets of models was described above.

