## 12.3 Sample Size Considerations

### 12.3.1 Primary Aim

A longitudinal mixed model will be used to compare the 12-month change in SPADI between treatment arms. The operating characteristics of this plan depend on the marginal distribution of  $\square\text{SPADI}_{12}$ , the assumed true distributional shift, and observed covariate patterns. Figure 3 displays the marginal distribution of  $\square\text{SPADI}_{12}$  for patients by treatment group. These distributions were derived from preliminary data taken from an ongoing prospective, non-randomized cohort of patient with degenerative rotator cuff tears receiving either non-operative or operative intervention. The mean  $\square\text{SPADI}_{12}$  was -16.7 (SD=24.2; n=72) overall. Current estimates for non-operative therapy are -12.3 (SD=21.55; n=45) and -40.6 (SD=19.14; n=27).

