### 12.3.2 Effect Size and Alternative Hypotheses

A 10 unit change in SPADI is the smallest clinically meaningful change. In Aim 1 we test the null hypothesis that  $\square\text{SPADI}_{12}$  for patients treated operatively versus non-operatively is equal. As shown below, a sample size of 700 provides outstanding power to detect a 10-unit difference between treatment arms in 12-month SPADI change from baseline.

[figure not shown]

Figure 3. Distributions of 12-month change in SPADI by treatment group.

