### 12.3.3 Sample Size Projections

A sample size of 700 participants (350 per treatment group) provides excellent power even with significant levels of dropout/lost-to-follow-up rate (a two-sided Type I Error of 0.05 was used). Figure 4 illustrates the power for three different tests of  $\Delta\Delta\text{SPADI}_{12}$ . The black line shows the power for a simple t-test of 12-month SPADI change scores between treatment groups. The red line shows the power for a least squared means Wald test of the 12-month SPADI change scores between groups, but adjusted for baseline

covariates (mixed model with complete case analysis). The blue line shows the power for the same test from the mixed model, but when multiple imputation is used to properly account for the large number of missing observations in the preliminary data (RVI is 0.53). Here, RVI is the average relative increase (averaged over all coefficients) in variance estimates due to missing values. The largest fraction of missing information (FMI) is 0.412. Interestingly, rather than gaining efficiency, the MI mixed

model appears less efficient. Because the MI model properly accounts for variability in the presence of missingness, we can use this model to anticipate a loss of power due to missing data. These curves are based on the estimated standard deviation from the preliminary data: (black) t-test on available data, (red) mixed model on complete case data, (blue) multiply imputed mixed model. The dotted line shows the power to detect the same minimally clinically meaningful change in binary subgroups across treatment groups (e.g., gender by treatment interactions). The standard deviations for these curves were similarly derived from preliminary data. This approach allows us to carefully leverage preliminary data to anticipate cluster correlation, covariate effects, missing data patterns, and longitudinal correlation patterns. These projections are conservative.

To be clear, power for the adjusted mixed model reaches 90% at 60 patients per group. With the increased variance from imputation, power reaches 90% with 82

[figure not shown]

**Figure 4.** Power curves for primary treatment comparison (solid lines) and interactions (dashed lines) from covariate adjusted

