patients in each treatment group. For the unadjusted t-test, 90% power is achieved with 91 patients per treatment group. For the subgroup/patient heterogeneity analyses, 80% power to detect a 2-way interaction as small as the MCID is achieved with 122 patients per group (total n=488) for the imputed data set. Consequently, we expect to have excellent power to detect heterogeneous treatment effects, even in the presence of significant missing data (FMI was 0.41). Lastly, we note that in our preliminary data, the intraclass correlation coefficient (ICC) for institution was 0.04 (essentially zero) and largely inconsequential given the longitudinal correlation in SPADI measurements. If necessary, our approach permits the sequestering of site-to-site variability from residual error, increasing power for detecting fixed effects in the data.

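### The displayed mixed model assumes one variance and one correlation across months 3, 6 and 12, which can mis-calibrate the standard error of the 12-month contrast

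*Protocol*

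**What the plan says.** Section 12.2.1 of the protocol writes out the primary model. The response is change in SPADI from baseline for participant i at months 3, 6 and 12. After the fixed effects come u_i and e_ij, described as follows: "The last 2 terms represent a patient specific random intercept to model the effects of study site and residual error, respectively". Section 12.2.2 repeats the structure for ASES-SF: "the last 2 terms represent a patient specific random intercept and residual error, respectively". The quantity reported from the primary model is a single-visit difference between arms, "typically estimated as a contrast or difference in predicted 12-month SPADI change".

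The section allows a non-linear or categorical time effect and splines for continuous covariates. A later paragraph of 12.2.1 adds a fixed or random site effect and says that the displayed equation does not show it. Section 12.4 promises residual checks, a proportional-odds cross-check and missing-data sensitivity analyses. No section names a residual covariance structure or a robust standard error for the primary test.

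**The concern.** A patient intercept plus independent, equal-variance residuals is compound symmetry. It has two variance parameters, so months 3, 6 and 12 share one variance and one pairwise correlation. For a change score this is a strong assumption. If the raw SPADI SD is constant, the variance of change at visit j is 2σ²(1 − ρ_j), where ρ_j is the correlation with baseline. Equal variances then need the same ρ_j at all three visits. If correlation with baseline fades, month 12 is the most variable visit. If recovery after surgery spreads the early scores, month 12 is the least variable.

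The calibration of the p-value and confidence interval for Hypothesis 1, and of the ASES-SF analysis, is at stake. With incomplete follow-up, a likelihood analysis also uses the assumed covariance to carry information from early visits to month 12, so a wrong covariance can move the estimate itself.

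**Working it through.** **Inputs from the protocol.** The test: "a two-sided Type I Error of 0.05 was used" (12.3.3). The difference of interest: "A 10 unit change in SPADI is the smallest clinically meaningful change" (12.3.2). SDs of 12-month change, 12.3.1: "Current estimates for non-operative therapy are -12.3 (SD=21.55; n=45) and -40.6 (SD=19.14; n=27". There are 350 patients per arm. SDs at 3 and 6 months, between-visit correlations and a trial dropout pattern are not given, so they are assumed below.

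**The plan's own figure.** Pooled SD = √[(44 × 21.55² + 26 × 19.14²)/70] = 20.69. For 90% power, n = 2 × (1.960 + 1.282)² × 20.69²/10² gives 90 per group, or 91 with the noncentral t. This agrees with 12.3.3: "For the unadjusted t-test, 90% power is achieved with 91 patients per treatment group". A month-12 SD near 20.7 is therefore a sound anchor.

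**Complete data, categorical time.** The model's variance for the month-12 mean is the average of the three visit variances. The true variance is that of month 12. With R = √(average variance)/SD₁₂, the type I error is 2 × [1 − Φ(1.96 R)].

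| Assumed SDs, months 3/6/12 | Average variance | Root | R | Type I error |
|---|---|---|---|---|
| 16.7/19.0/21.0 | (278.9 + 361.0 + 441.0)/3 = 360.3 | 18.98 | 0.904 | 7.6% |
| 14/17/20.7 | (196 + 289 + 428.5)/3 = 304.5 | 17.45 | 0.843 | 9.8% |
| 24/22/20.7 | (576 + 484 + 428.5)/3 = 496.2 | 22.27 | 1.076 | 3.5% |
| 20.7 at each visit | 428.5 | 20.70 | 1.000 | 5.0% |

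The first row corresponds to a raw SD of 20 and baseline correlations of 0.65, 0.55 and 0.45, since 2 × 400 × (1 − ρ) gives 280, 360 and 440.

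**Linear time.** The weights at month 12 are (−0.143, 0.214, 0.929), so between-visit correlations also enter. Simulated results were close to those for categorical time: with SDs 14/17/20.7, the model SE was 1.30 against an empirical 1.54.

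**Simulation, 600 trials of 350 per arm, categorical time, complete data.** The simulation margin around 5% is about ±1.7 points.

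- SDs 14/17/20.7: model SE 1.32, empirical 1.56, rejection 10.5%.
- SDs 24/22/20.7: model SE 1.68, empirical 1.52, rejection 3.7%.
- Equal SDs, correlation decaying by a factor of 0.8 per 3 months: model SE 1.56, empirical 1.57, rejection 4.2%. Unequal correlation alone left the SE essentially right.

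**About 20% dropout depending on observed scores.**

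- Same mechanism in both arms: bias at most 0.13 points in every scenario. With decaying correlation and equal SDs, the model SE was somewhat small (1.67 against 1.76 to 1.79).
- Opposite directions by arm, covariance truly compound symmetric: no bias.
- Opposite directions by arm, covariance not compound symmetric: bias of 0.6 to 1.9 points, of either sign, and type I error of about 8.5% to 19.5%.
- Unstructured covariance, same scenarios: bias at most 0.12 points.

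**Loss in the non-operative arm only, worse scores leaving earlier** (first-row SDs, assumed correlations). Compound symmetry gave bias of about 0.3, 0.4 and 0.6 points at 8%, 18% and 26% lost. Unstructured stayed within 0.1.

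**The case against.** The protocol never says that e_ij is independent with constant variance, and a random intercept can be combined with structured residuals. A statistical analysis plan, not seen here, is a normal place for that detail. This has some force. Even so, 12.2.1 presents a specific model as the primary one, and the ordinary reading of its two random terms is compound symmetry. A later plan with another covariance would depart from what is displayed, and the wording would still need aligning.

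The residual checks, proportional-odds cross-check and missing-data analyses in 12.4 are real safeguards. They might reveal unequal variances, but none comes with a rule that changes the primary test. Section 12.3.3 computes power for a multiply imputed mixed model. If imputation were used for the primary analysis, the dropout argument would not carry over directly, but the protocol does not make imputation primary.

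A reader might infer that the 12-month standard error is wrong as planned, and that any dropout will bias the estimate. The documents do not support either statement. They give no visit-specific SDs, correlations or dropout pattern. With equal variances and complete data the test is nominal, and dropout with the same mechanism in both arms gave almost no bias.

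Dropout that differs by arm is plausible but not shown. The trial is unblinded, and 5.3.2 expects crossover mainly from non-operative to operative treatment. The second analysis in 12.4 treats crossovers as dropouts at crossover, which would make the loss largely one-armed. That is a sensitivity analysis, not the primary test.

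**Conclusion.** The concern stands in conditional form. The displayed models in 12.2.1 and 12.2.2, read in the usual way, fix a restrictive covariance that no other passage relaxes. With complete data, the 12-month standard error is mis-calibrated to the extent that the month-12 variance differs from the average over visits. Neither size nor direction can be derived from the protocol. The range of about 3.5% to 10% for a nominal 5% test rests entirely on the assumed SDs. Bias of about 0.3 to 2 points, at most roughly a fifth of the 10-point difference of interest, needs both a covariance that is not compound symmetric and outcome-dependent dropout that differs by arm.

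This is a matter of calibration, not power: at 350 per arm and an SD of 20.69, power for 10 points is above 99.9% with complete data or 20% loss, and 99.8% with 41% loss.

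One fault does not depend on assumptions. A participant-level u_i cannot represent study site, and the same section says that the site effect is not in the displayed equation. The two statements must be reconciled. The change is worth making because it protects the primary test whichever way the variances run.

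**What to change.** In 12.2.1 and 12.2.2, replace the random intercept and independent residuals by an unstructured 3x3 residual covariance over the nominal visits. Use categorical time and Kenward-Roger or Satterthwaite degrees of freedom. State a fallback for non-convergence: heterogeneous Toeplitz, or the random-intercept model with robust standard errors. Section 7.4.1 says that actual completion dates will be taken into account; a sensitivity analysis can do this. Keep site as a separate, displayed term and remove the statement that u_i models site.

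The cost is wording and four extra covariance parameters (six instead of two), which is negligible with 700 patients. With complete data and visit-specific means, the unadjusted 12-month contrast equals the simple 12-month comparison, so the plan's 91 per group still applies and the sample size is unchanged.
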